#### Number of participants

We will recruit 12,000 participants, from approximately 170 general practices.

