### Management of the visits

Based on the test’s reported 90% specificity and 41% sensitivity we anticipate that 520–550 participants in the intervention arm will have a positive test result. These will be offered a chest X-ray in accordance with local requirements for prioritisation and will be referred for a non-contrast thoracic CT scan. If there is a suspicious opacity on the chest X-ray or initial CT scan a contrast enhanced staging CT will be undertaken. As a quality control measure no participant undergoing CT screening in the test positive arm will have all their 5 CTs reported by same radiologist. Nodule size will be currently reported as the mean of 2 diameters at 90° angles, volumetric analysis is starting soon on both sites with diameter and volume to be reported. If the initial CT scan reveals no evidence of lung cancer then subsequent CT scans will be offered 6 monthly for 24 months. An appointment window of ± 4 weeks will be initiated for each scheduled CT scan.

If a test positive participant has had a chest X-ray in the previous 1 month, or a CT scan in the previous 3 months, these can be reviewed as part of the study. With the participant’s consent chest X-rays or CT scans prior to study entry will be retrospectively coded. The participant will proceed to have the series of up to 5 CTs.

Participants will receive appointments via post/email, according to patient preference. Participants will be called 2–4 days before each CT scan appointment. Individuals with abnormalities as classified by the radiology/respiratory physician’s study panel on baseline CT scan or subsequent CT scan will be followed up over the study period or referred for NHS clinical care as appropriate. All individuals entering the study will be flagged and followed-up via the Scottish Cancer Registry in the Electronic Data Research and Innovation Service (eDRIS) [26]. Participants who develop lung cancer will be followed-up via their medical records to assess both time to diagnosis and stage of disease at diagnosis. If no histological stage is available, stage will be assessed by a panel of three respiratory physicians blind to allocation status of the study subjects from chest X-rays or CT, or if no imaging is available, medical assessment of stage will be carried out.

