#### Secondary

numbers at 24 months after randomisation, in the different stages at diagnosis (III/IV/U/other) in the intervention arm and the control arm;difference, after 24 months, between costs and outcomes between the intervention arm and in the control arm and cost-effectiveness of the test compared to standard practice;differences, after 24 months, of lung cancer mortality, all-cause mortality and cancer-specific mortality rates between the intervention arm and in the control arm;differences, after 5 and 10 years, of long-term future mortality rates in the intervention arm and in the control arm;differences, after 24 months in (i) the number of patients with stage III, IV or unclassified lung cancer at diagnosis in the test-positive group and those in the test-negative group and (ii) stage at diagnosis in the test-positive and test-negative group;difference between the test-positive, test-negative groups and the control arm at 1, 3, 6, and 12 months in scores for EQ5D [29], Positive and Negative Affect Schedule [30], revised Illness Perception Questionnaire adapted to refer to lung cancer and lung cancer risk [31], Lung cancer risk perception, Health anxiety subscale of Health Orientation Scale [32], the Adapted Lung Cancer Worry Scale [33] and Impact of Events Scale [34] (for the test-positive group, the test-negative group only) and differences in smoking behaviour and health service use. Long-term scores for the same outcomes for the test-positive group at 18 and 24 months;difference in incidence at 24 months, and after 5 and 10 years, in other clinical measures such as Cerebrovascular disease, Chronic Obstructive Pulmonary Disease, hospital stays, and outcomes identified through the Scottish Morbidity Record (SMR) linkage in the intervention arm and in the control armnumbers in all groups at 24 months (test-positive, test-negative and control) undertaking subsequent investigations such as chest X-ray, CT and bronchoscopy (Table 1)

**Table 1 Tab1:** Data Collection Timeline

Assessment/Procedures	Timeline (± 2 weeks)				
	Visit 1 (~30-45mins)		Visit 2 (~30mns)	➢ *EarlyCDT Positive Test Participants may visit or call.* ➢ *EARLY CDT Negative Test Participants may attend for further information/advice only.*	
*Informed Consent*	X				
*Inclusion/Exclusion Criteria*	X				
• *Review/Record only Relevant Medical History relating to IC/EC*	X				
• *Review/Record Relevant Medications* • *Relating to IC/EC*	X				
*Blood Sample*	X				

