### Statistics and data analysis

#### Sample size calculations

##### Main study

The rate of lung cancer was 187/100,000 per year for patients aged 50–74 in Scotland 2008 which is higher than many other similar countries [23]. Deprivation is associated with a significantly higher risk of lung cancer. Living in the most deprived quintile is associated with an increased risk of 1.8 times compared to the middle quintile of deprivation; this gives an estimated annual lung cancer rate of 336/100,000 among the practices taking part in the study. A high risk group within this population will be selected using similar entry criteria (outlined above) as the Mayo screening study which had a 2% prevalence rate of lung cancer and a further 2% incidence rate over the following 5 years [35]. The baseline rate of late stage presentation for the particular high risk population envisaged in this study is uncertain, as is the size of the reduction in late stage presentation likely to be achieved through use of EarlyCDT®-Lung Test. Using an estimated late stage presentation rate of 1,200/100,000 per year in the control arm i.e. 2.4% over the 2-years follow-up period, provides 85% power at 5% significance (two-sided) to detect an estimated reduction of 35% in late stage presentation rate in the intervention arm i.e. as low as 780/100,000 per year or 1.56% over the 2-years follow-up period. This corresponds to an estimated event rate over the 24 months of follow-up of 120 events in the control arm and 78 events in the intervention arm and implies a required sample size of 5,000 per arm i.e. a total of 10,000 participants.

The anticipated 35% reduction in event rate between the control arm and the intervention arm was justified by current estimates of the capability of the test to identify cases together with current estimates of the sensitivity of CT scanning (67%). The assumed event rate in the study participants of 1.2% per year was an estimate and the sample size would be modified if the observed event rate proves to be markedly different, acknowledging the a priori possibility that we will employ a prospective adaptive design. No Interim analysis of efficacy is planned.

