### Proposed analyses

Characteristics of participants will be compared informally between treatment arms at baseline. The main analysis of the primary outcome will be intention-to-treat. Cox proportional hazards models which will be used to estimate the hazard ratio of the rate of late stage lung cancer in the intervention arm compared to the control arm. Participants who are lost to follow up will be censored. The models will adjust for age, gender smoking history, socioeconomic status and practice. If appropriate, random cluster effects will be included rather than fixed effects for practices. A similar methodology will be used for the secondary outcomes of comparisons of mortality rates. A subsequent analysis will compare the outcomes of those with a positive test in comparison to those in the intervention group with a negative test (primary contrast for this analysis) and those in the control group. Comparisons of proportions will be carried out using chi square tests. Fisher’s exact test will be used if the number of events is small.

Psychological and behavioral outcomes will be compared between the three groups (Test-positive, Test-negative and the control group) at baseline using analysis of variance (or non-parametric tests if there is evidence of non-normal distribution of scores) for continuous measures and *χ*
^2^ tests for categorical measures. Psychological (HADS Score) and behavioral measures will be described at each follow up time point and multilevel regression models will be used for analyses to take account of repeated measurements during follow up [38].

Poisson regression models, adjusting for follow up time if necessary, will be used to investigate the other clinical measures (secondary outcomes 7 and 8).

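### Poisson regression is named for secondary outcomes 7 and 8 with no provision for overdispersion, which suits recurrent hospital stays poorly

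*Protocol article*

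**What the plan says.** Under Proposed analyses, the Protocol article assigns one model to the last two secondary outcomes: "Poisson regression models, adjusting for follow up time if necessary, will be used to investigate the other clinical measures (secondary outcomes 7 and 8". Follow-up time is the only contingency attached to it.

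The secondary outcomes are not numbered in the article, so 7 and 8 are taken from the order of the list.

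- **Outcome 7** compares the arms on incidence "in other clinical measures such as Cerebrovascular disease, Chronic Obstructive Pulmonary Disease, hospital stays", together with other outcomes found through record linkage, at 24 months and at 5 and 10 years.
- **Outcome 8** is the numbers "in all groups at 24 months (test-positive, test-negative and control) undertaking subsequent investigations such as chest X-ray, CT and bronchoscopy".

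No event rate, dispersion, power or variance estimator is given for either. Under Safety assessments, the article says that more ill-health than usual is to be expected, because of the participants' age and co-morbid conditions.

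**The concern.** Outcome 7 mixes two kinds of data. A first diagnosis of chronic obstructive pulmonary disease or cerebrovascular disease happens at most once per person. A hospital stay can happen many times, and stays tend to concentrate in the sickest participants.

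The default Poisson standard error assumes that the variance of the count equals its mean, given the covariates in the model. That holds for recurrent stays only if participants with the same covariates share one underlying rate and their stays are independent. With eligible ages from 50 to 75, performance status 0 to 2 and acknowledged co-morbidity, this is unlikely. The variance will very probably exceed the mean, and default errors will then be too small.

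Hospital stays are part of the evidence on the downstream burden of the screening strategy. An interval that is too narrow could turn chance variation between arms into an apparent harm or benefit.

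**Working it through.** The article gives no figure for these outcomes, so there is nothing to reproduce. The check asks how far default Poisson errors mislead for a given departure from variance = mean.

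**Inputs**
- Significance level: 5% two-sided. The article states this for the primary outcome ("85% power at 5% significance (two-sided", Sample size calculations); it is assumed here for outcomes 7 and 8.
- Sample size: "We will recruit 12,000 participants, from approximately 170 general practices" (Number of participants), taken as 6,000 per arm with 1:1 allocation.
- Variance-to-mean ratio, φ: not in the article. Assumed values of 1.5, 2 and 3 are shown, with φ = 1 as reference.

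**Recurrent counts.** If the true variance is φ times the mean, the correct standard error is √φ times the Poisson one. The actual two-sided type I error is 2 × [1 − Φ(1.96/√φ)], and the actual coverage of a 95% interval is one minus that.

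| φ (assumed) | √φ | 1.96/√φ | Type I error | Coverage |
|---|---|---|---|---|
| 1 | 1.00 | 1.96 | 5.0% | 95.0% |
| 1.5 | 1.22 | 1.60 | 11.0% | 89.1% |
| 2 | 1.41 | 1.39 | 16.6% | 83.4% |
| 3 | 1.73 | 1.13 | 25.8% | 74.2% |

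A simulation with negative binomial counts, 6,000 per arm, 20,000 replicates and a Wald test on the log rate ratio agrees: 10.7% at φ = 1.5, 16.5% to 16.7% at φ = 2, and 25.7% at φ = 3.

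**Effect of longer follow-up.** If individual rates vary with squared coefficient of variation CV², then φ = 1 + CV² × mean count, so φ rises as stays accumulate. As an illustration only, take CV² = 1:
- a mean of 0.6 stays gives φ = 1 + 0.6 = 1.6 and a type I error of about 12%;
- a mean of 3 stays gives φ = 1 + 3 = 4 and about 33%.

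Neither the means nor the CV² come from the article. The direction matters because outcome 7 is also to be compared at 5 and 10 years.

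**Person-level yes/no outcomes.** Here the variance is p(1 − p) against a mean of p, so φ = 1 − p and the default error is too large by 1/√(1 − p). The same formula gives:

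| p (assumed) | Type I error |
|---|---|
| 0.01 | 4.9% |
| 0.05 | 4.4% |
| 0.10 | 3.9% |
| 0.30 | 1.9% |

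Simulated values at 0.05, 0.10 and 0.30 are 4.5%, 4.0% and 2.0%. The error is conservative. It is negligible for rare outcomes and clear only for common ones.

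**The case against.** The strongest reply is that the article names a model family and not a variance estimator. Poisson regression with robust or scaled errors is still Poisson regression, and the handling of overdispersion is ordinary content for the statistical analysis plan, which the article mentions and which is not shown. This stands in part: the article does not require default errors, and the unseen plan may already deal with the matter. It does not remove the point. The article positively names a model whose default variance does not suit recurrent stays. The same section does provide for other awkward data: non-parametric tests for skewed scores, an exact test for few events, and multilevel models for repeated questionnaires.

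Three stronger readings are tempting, and the documents do not support them.

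- **All results for outcomes 7 and 8 will be wrong.** They may not be. The error depends on which variance estimator is used and on a dispersion that the article does not give. Rare yes/no conditions are barely affected. Outcome 7 is framed as incidence, so even stays might be analysed as any admission versus none, in which case default errors would be conservative.
- **The CT schedule makes outcome 8 heavily overdispersed.** Test-positive participants are offered a CT series ("The participant will proceed to have the series of up to 5 CTs"), so pooling scans across the whole intervention arm would give a very uneven count. But outcome 8 as worded most naturally counts persons, not scans, and it keeps test-positive and test-negative participants apart. Within the test-positive group the number of scheduled scans is capped, which points away from overdispersion.
- **The trial's main conclusion is at risk.** It is not. The primary outcome and the mortality comparisons use Cox models, and the psychological outcomes use multilevel models.

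The section also provides chi-square tests for comparing proportions, which would be a valid route for person-level outcomes. That leaves outcome 8 with two candidate methods but does not help recurrent stays.

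**Conclusion.** The point holds for hospital stays and is minor. If stays are modelled as counts with model-based Poisson errors, the intervals will very likely be too narrow. At assumed variance-to-mean ratios of 1.5, 2 and 3, a nominal 5% test rejects about 11%, 17% and 26% of the time, and 95% intervals cover about 89%, 83% and 74% of the time. These figures assume a 5% two-sided level for secondary outcomes; the true ratio is unknown, and any covariates in the model would lower it. For person-level outcomes, including outcome 8 as worded, the only consequence is some conservatism when the outcome is common.

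**What to change.** Extend the sentence in Proposed analyses, or settle it in the statistical analysis plan, as follows:

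1. Use robust (sandwich) standard errors for the Poisson models of outcomes 7 and 8. This corrects intervals that are too narrow for recurrent counts and intervals that are too wide for common yes/no outcomes.
2. For hospital stays counted as recurrent events, use negative binomial regression, or Poisson regression with robust errors.
3. State that outcome 8 counts persons, and whether hospital stays are counted per event or per person.

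The cost is a sentence or two and a software option. The downside is wider intervals for hospital stays: relative to default Poisson errors, by a factor of about 1.22, 1.41 or 1.73 at ratios of 1.5, 2 or 3. At a ratio of 1 nothing changes.

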### Cost effectiveness analysis

A short-term within-trial analysis will compare the costs and outcomes associated with the intervention arm to those of the comparison arm at 24 months, with a focus on cost-per-case detected. A longer term analysis will employ a decision analytic model to link the short term outcomes measured within the trial to potential longer term impacts on health, in terms of impacts on morbidity and mortality of early detection and treatment, to allow the estimation of cost-per Quality Adjusted Life Years gained. Both analyses will take the perspective of the NHS and personal social services and conform to the reference case favoured by NICE [39].

### Missing data

The extent of missing data will be examined and, if necessary, methods such as multiple imputation will be implemented to assess the robustness of results to missing data, assuming data are missing at random.

#### End of study

The end of study is defined as last patient last visit test-related scan plus 24 months. The Sponsor, CI and/or the Trial Steering Committee have the right at any time to terminate the study for clinical or administrative reasons.

### Data collection & management

#### Data collection

All research blood samples will be transported to the University of Nottingham for processing, and then transported to the US for Test processing by Oncimmune. All samples will be stored under custodianship as per UK Biobank guidelines [40]. Sample Analysis and Chain of Custody Plans are documented in the Study Operations Manual. The participant’s medical notes (GP and hospital) paper or electronic will act as source data for relevant past medical history, subsequent medical conditions, hospital admissions and diagnostic reports.

Psychological and behavioural data will be collected on the first 10,000 participants through a baseline questionnaire administered during Visit 1. Follow-up data will be collected between 1 and 12 months on subsets of the intervention and control arms and at 18 and 24 months for the EarlyCDT®-Lung Test-positive group. Data collected at baseline will include the EQ5D, Hospital Anxiety and Depression Scale, Positive and Negative Affect Schedule, revised Illness Perception Questionnaire adapted to refer to lung cancer and lung cancer risk, lung cancer risk perception, items from the Health Orientation Scale, the adapted Lung Cancer Worry Scale, smoking behaviour and demographic details. Follow-up questionnaires include the same measures, plus health service use and Impact of Events Scale and health service use for those who had the test. The Hospital Anxiety and Depression Scale is not included in follow-up questionnaires and the EQ-5D is not included in the 3 months follow-up questionnaire.

All participants in the positive group will be approached with the recruitment aim of 300 from this group. The TCTU will use an electronic randomisation tool to randomly sample patients from the test-negative group and control arm, stratified by the two study centres. Twenty-one individuals will be sampled each week and invited to complete follow-up questionnaires with an aim of recruiting 300 from both groups (based on an anticipated response rate of 67%).

Participants who receive a diagnosis of lung cancer will not be followed up subsequent to receiving the diagnosis.

### Data management and data management system

Data will be collected by the RN either directly onto a paper CRF with subsequent transcription to the eCRF, or direct data entry onto the web based eCRF.

TCTU will provide a data management system using OpenClinica [41]. The data management system will be fully validated, including the provision of test data and supporting documentation. Backup and disaster recovery will be provided by TCTU according to its standard operating procedures [42].

The Statistical Analysis Plan will specify dummy tables linked to primary and secondary outcomes and the data management system will be designed to export directly to the dummy table formats for analysis.

#### Safety assessments

Adverse Events (AE) and Serious Adverse Events (SAE) will be recorded. A number of factors affecting the trial population suggest that we would expect to observe a larger than normal incidence of episodes of ill-health due to both the age and co-morbidities of the study population. All chest X-ray and CT scan incidental findings will be recorded in the CRF as an incidental finding and a specialist referral will be made as directed in a study Standard Operating Procedure (SOP) within the Study Operations Manual [43]. AEs (as defined) will be recorded as soon as they are known either from the study subjects, PI patient review audits or via SMR or record review.

### Ethical considerations

The study will be conducted in accordance with the principles of good clinical practice (GCP) and the Research Governance Framework Scotland [44].

### Confidentiality

All records will be kept in a secure storage area with limited access to study staff only. Clinical information will not be released without the written permission of the participant, except as necessary for monitoring and auditing by the Sponsor, its designee or Regulatory Authorities.

#### Data protection

The CI and study staff involved with this study will comply with the requirements of the Data Protection Act 1998 with regard to the collection, storage, processing and disclosure of personal information and will uphold the Act’s core principles. The CI and study staff will also adhere to the current version of the NHS Scotland Code of Practice on Protecting Patient Confidentiality and all other governance requirements. Published results will not contain any personal data that could allow identification of individual participants.

#### Insurance and indemnity

The University of Dundee and Tayside Health Board are Co-Sponsoring the study.

## Discussion

Despite advances in surgical techniques, radiation therapy and systemic therapy the outlook for patients with lung cancer has improved more slowly than many other cancers over the last 50 years. Early diagnosis of treatable disease is likely to be the major way of changing outcomes for the foreseeable future. The study will assess the EarlyCDT®-Lung Test’s clinical suitability and cost effectiveness for a large-scale, accredited screening service for early lung cancer detection. It will also assess potential morbidity arising from the test and potential psychological and behavioural harms and benefits of test results.

The major strength of this trial lies within its design. By being both randomised and controlled many of the inherent biases that affected many of the previous screening studies will be removed. Our trial will also be able to investigate the effect of either a positive or negative result on participants’ lifestyle decisions to explore whether a negative result reinforces harmful behaviour, such as smoking, or a positive result reduces harmful behaviour. To date, screening with low dose CT scanning does not appear to have a beneficial effect on smoking behaviour [38, 45–47]. As in many screening studies a potential weakness is that the study population may be different to the usual clinical populations in terms of age, smoking status and education. Our eligibility criteria ensure participants have a high risk of lung cancer over the subsequent 24 months and our findings should be generalisable to populations with a similar level of risk. Our focus on areas with high levels of deprivation for recruitment should help ensure our participants reflect the social gradient in lung cancer incidence and our collection of demographic data will enable us to compare the characteristics of our trial population with those at risk of lung cancer.

One potential weakness is that participants randomised to the control arm may change their behaviour to decrease their risk of lung cancer e.g. by stopping smoking in a way that they would not have done had they not been participating in our study. The lack of impact of screening using CT scanning on smoking behaviour suggests this may not occur to an important extent, but measurement of smoking behaviour at repeated follow up time points will enable us to quantify this and assess its impact on our findings.

